# The effects of probiotics administration on the gut microbiome in adolescents with anorexia nervosa—A study protocol for a longitudinal, double‐blind, randomized, placebo‐controlled trial

**DOI:** 10.1002/erv.2876

**Published:** 2021-11-30

**Keywords:** anorexia nervosa, gut microbiome, gut–brain axis, probiotics, randomized controlled trial

## Abstract

**Objective:**

Knowledge on gut–brain interaction might help to develop new therapies for patients with anorexia nervosa (AN), as severe starvation‐induced changes of the microbiome (MI) do not normalise with weight gain. We examine the effects of probiotics supplementation on the gut MI in patients with AN.

**Method:**

This is a study protocol for a two‐centre double‐blind randomized‐controlled trial comparing the clinical efficacy of multistrain probiotic administration in addition to treatment‐as‐usual compared to placebo in 60 patients with AN (13–19 years). Moreover, 60 sex‐ and age‐matched healthy controls are included in order to record development‐related changes. Assessments are conducted at baseline, discharge, 6 and 12 months after baseline. Assessments include measures of body mass index, psychopathology (including eating‐disorder‐related psychopathology, depression and anxiety), neuropsychological measures, serum and stool analyses. We hypothesise that probiotic administration will have positive effects on the gut microbiota and the treatment of AN by improvement of weight gain, gastrointestinal complaints and psychopathology, and reduction of inflammatory processes compared to placebo.

**Conclusions:**

If probiotics could help to normalise the MI composition, reduce inflammation and gastrointestinal discomfort and increase body weight, its administration would be a readily applicable additional component of multi‐modal AN treatment.

AbbreviationsANanorexia nervosaBMIbody mass indexDSM‐5Diagnostic and Statistical Manuel Of Mental Disorders—5th versionICD‐10International Classification of Diseases and Related Health Problems—10th revisionITTintention to treatMImicrobiomePUFApoly‐unsaturated fatty acids

## INTRODUCTION

1

Anorexia nervosa (AN) is a complex and serious mental disorder characterised by a distorted body image, fear of gaining weight, extreme dietary restriction accompanied by severe weight loss and psychiatric comorbidities (American Psychiatric Association, 2013). A recently published meta‐analysis show that eating disorders including AN have a high prevalence worldwide (pooled mean prevalence for AN: 1.4%, range: 0.1%–3.6% for females) and indicate an increase of the point prevalence of eating disorders over the recent years (Galmiche et al., 2019). In the Mental Health in Austrian Teenagers study a lifetime prevalence of 3.73% for any eating disorders and a prevalence of 1.44% for AN was found in 10–18‐year‐old adolescents (Wagner et al., 2017).

The treatment of AN often succeeds in temporarily restoring weight, but the starvation process in AN is often self‐perpetuating and patients have a high risk for an early relapse (Carter et al., 2012) and a chronic enduring course despite intensive treatment efforts (Wonderlich et al., 2020). Recovery of normal body weight, as one of the key elements in the treatment of AN, is often associated with gastrointestinal discomfort (GID) and abnormal fat distribution. These consequences of change can cause recurrent weight loss and could make them more prone to relapse, and may contribute to a chronic course of this illness (El Ghoch et al., 2016).

Recent studies on the gut‐brain‐interaction provide a promising basis to develop innovative interventions for patients with psychiatric illnesses (Bambury et al., 2018)*,* in particular for AN. Previous research has already identified the important link between the gut‐microbiome (MI) and the regulation of body weight (Smith et al., 2013)*,* on one hand, and psychological states, such as anxiety and depression (Pirbaglou et al., 2016)*,* on the other hand. There is growing evidence that the typical features of AN, malnutrition and long‐term unhealthy altered diet, have a profound influence on the MI (Herpertz‐Dahlmann et al., 2017; Mack et al., 2018). A recent study on adolescents with AN indicates that alterations in gut microbiota do not normalise with weight restoration (Schulz et al., 2021). Moreover, endocrinological consequences are primary or secondary amenorrhoea which occurs due to the lack of oestrogen (Neuman et al., 2015). This fact in turn leads to other problems, since difficult‐to‐treat patients are often medicated with olanzapine, which together with oestrogen have a significant impact on the MI (Maier et al., 2018; Neuman et al., 2015). Recent studies provided further evidence for a significant intestinal dysbiosis in AN, which was only partially improved with weight gain, for example, lower abundances of Bacteroidetes and carbohydrate utilising taxa as well as higher abundances of Firmicutes and Verrucobacteria. The latter two can increase intestinal wall permeability via mucin degrading and protein fermenting, which can further contribute to a ‘leaky gut’ syndrome and trigger an immune‐response (Mack et al., 2016).

Research on the gut‐brain axis is of particular relevance considering the neurological changes and neuropathological symptoms associated with AN. The morphology of the brain in patients with AN shows a change in form of a loss of volume in grey and white matter even in early stages (Seitz et al., 2016). These findings are linked to deficits in neuropsychological functioning (Seitz et al., 2015). Specifically, the MI has been previously linked to the reward system. In neuropsychological and neuroimaging studies it could be shown that patients with AN respond differently to reward and punishment in comparison to healthy controls, which may also explain their maladaptive response to hunger (DeGuzman et al., 2017). Findings from the activity based anorexia nervosa (ABA) animal model, which combines food restriction and running wheel availability confirm that animal models of AN have an striking reduction of astrocytes (Frintrop, Liesbrock, et al., 2018) and reduced cell neogenesis. Similar to phenomena in human AN weight loss, hyperactivity, amenorrhoea, hormonal disturbances, learning deficits and brain volume loss have been shown (Frintrop, Trinh, et al., 2018). Recently, intestinal dysbiosis was also confirmed in the ABA animal model, which was associated with the described brain volume and astrocyte‐marker alterations (Trinh et al., 2021).

A significant progress has been made in the field of studies on probiotic interventions. Remarkable effects on brain cell neogenesis were shown by the use of antibiotics and probiotics in mice model. While antibiotics induce a sustainable decrease in neogenesis, the treatment with probiotics leads to an increase of neogenesis (Möhle et al., 2016). As such pre‐clinical trials continue to show health benefits the administration of probiotics, sometimes also called psychobiotics, has been regarded as an option for develop innovative therapeutic intervention (Kelly et al., 2015).

As reported in the review by Markowiak and Slizewska (2017), the beneficial effects of probiotics on various diseases is known evident, particularly in the field of gastroenterology, but also in the field of allergology and infectiology, oncology and cardiology. Numerous studies have been published, particularly with regard to the selection and properties of individual probiotic cultures, their possible uses and their effects on health. Their main advantage is the effect on the development of the microbiota by ensuring a good balance between pathogens and bacteria that are necessary for the normal functioning of the organism. Probiotics can effectively inhibit the development of pathogenic bacteria such as *Clostridium perfringens*, *Campylobacter jejuni*, *Salmonella Enteritidis*, *Escherichia coli*, various types of *Shigella*, *Staphylococcus*. In addition, they increase the efficiency of the immunological system, improve the absorption of vitamins and minerals, stimulate the formation of organic and amino acids and can thus contribute to the prevention and treatment of various diseases (Markoviac & Slizewska, 2017). Specifically, probiotics interventions were tested in individuals with a variety of gastrointestinal symptoms whereby beneficial effects regarding improvements of gastrointestinal complaints were observed in about half the studies (Hungin et al., 2018).

With regards to mental health, preliminary clinical evidence suggests that the administration of probiotics could have beneficial effects in healthy individuals including significant improvements in positive affect and depressive mood and regarding significant changes in functional connectivity (e.g., in the salience network) as found in neuroimaging assessments (Bagga et al., 2018; 2019). In a sample of healthy college students, it was shown that multispecies probiotics improved panic anxiety, neurophysiological anxiety, negative affect, worry and mood regulation (Tran et al., 2019).

The effect of probiotic interventions have been also evaluated in patients with psychiatric disorders, including patients with major depression disorder, schizophrenia, bipolar disorder and Alzheimer disease (Amriani et al., 2020; Sanada et al., 2020). These studies indicate that probiotics supplementation may be effective in reducing symptoms of mental health disorders such as depression; however, the number of existing studies is still limited and definitive conclusions cannot be drawn. A systematic review on the impact of prebiotic/probiotic supplementation in children and adolescents with neuropsychiatric disorders including patients diagnosed with attention‐deficit/hyperactivity disorder and autism spectrum disorder, revealed significant improvements in the gut microbiota and behavioural changes (e.g., increased prosocial behaviour in autism spectrum disorder) (Ligezka et al., 2021).

Although profound alterations in the gut MI of patients with AN are evident (Di Lodovico et al., 2021) qualifying these patients as candidates to explore the effects of probiotics supplementation, no studies have evaluated the use of probiotics in the treatment of AN, so far. Thus, the aim of this study is to investigate the beneficial effects of a multistrain probiotics administration for 6 months in adolescent patients with AN. After treatment with probiotics, we expect alterations in the MI approaching composition of healthy‐weight individuals, improvement of gastrointestinal complaints and of depressive symptoms, a reduction of inflammatory processes and support weight gain post intervention and at 1‐year follow‐up. Probiotics may serve as a novel treatment component that minimizes the risk of relapse and a chronic course for this serious disorder of youth.

## METHODS

2

### Objectives and hypotheses

2.1

This study will investigate the clinical efficacy of administration of probiotics (in addition to treatment as usual, TAU) for 6 months in hospitalised adolescents with AN compared with placebo and follow them up at 6 months and 1 year. The core focus of this study is to evaluate whether probiotic supplementation support weight gain, improve eating disorder psychopathology, other psychopathology and gastro‐intestinal symptoms.

Specifically, our primary and secondary hypotheses are as follows.

#### Primary hypothesis

2.1.1

Patients with AN who receive a probiotic supplementation for 6 months show greater weight gain compared to patients who receive placebo.

#### Secondary hypotheses

2.1.2

Patients with AN who receive probiotics show a greater reduction in psychopathology which includes eating disorder pathology, depression, anxiety and obsessive‐compulsive behaviour compared to patients who receive placebo.Patients with AN who receive probiotics show a greater reduction in gastrointestinal complaints compared to patients who receive placebo.The composition of the gut MI of patients with AN who receive probiotics gets closer to the MI of healthy individuals compared to patients with AN who receive placebo.Patients with AN who receive probiotics show improved neuropsychological functioning (including cognitive flexibility, executive functioning, sustained attention) compared to patients who receive placebo.

Furthermore, associations of the MI with structural and functional brain‐imaging, serum (e.g., IgG, inflammatory markers, hormones), neuropsychology and psychopathology will be explored. Details regarding the acquisition and analysis of brain‐imaging data will be reported in a separate protocol paper.

In addition, the interactions of the MI and inflammation markers, gut permeability and hormones are tested to study their role in the potential anti‐inflammatory effect of probiotics in AN. Our hypotheses are that probiotics will influence the gut–brain axis in AN by an anti‐inflammatory effect mediated by the MI.

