### Inclusion and exclusion criteria

2.4

Inpatients aged 13–19 years, who are admitted to the Eating Disorders Unit at the Departments of Child and Adolescent Psychiatry, Medical University Vienna and Medical University of Innsbruck with the diagnosis of AN (307.1) or atypical AN (307.59) according to DSM‐5 will be eligible for the study. Written informed consent from participants and one legal representative, if patients are younger than 18 years, are required. Patients with comorbid disorders including organic brain disease, psychotic or bipolar disorder, substance use disorder, serious self‐injury, diabetes, those with insufficient knowledge of the German language, and those who used antibiotics during the last 6 weeks will be excluded. Further exclusion criteria are pregnancy and organic disorders with impact on the gastrointestinal tract (e.g. inflammatory bowel disease, coeliac disease). Previous operations on the gastrointestinal tract will be evaluated in the individual case. The same inclusion and exclusion criteria apply to the healthy controls; however, they have to be absent from any current diagnosed psychiatric disorder and current or lifetime eating disorder.

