### Statistical analysis plan

2.13

The primary analysis will be based on the intention‐to‐treat principle (ITT), including all randomized patients irrespective of the amount of treatment actually received. A per‐protocol analysis will be performed as sensitivity analysis. In order to follow ITT principle as closely as possible, all participants will be asked to participate in the end‐of‐treatment and follow‐up assessment (at 6 months and 1 year), in particular regarding BMI measurement, even if they drop out of treatment, to minimise the amount of missing data.

We will test for a difference in the primary outcome measure (age‐adjusted BMI at 1 year follow‐up) between the probiotics and placebo arm using a mixed‐effects model repeated measures analysis with covariates study site, sex, atypical/typical AN, and BMI at admission and will include any available further measurements of BMI (in particular at discharge and month 6). As this is equivalent to a phase II trial, emphasis will be on the 95% confidence intervals of the effect size estimates; additionally, *p*‐values will be calculated.

Secondary outcomes such as eating disorder pathology and changes in the gut MI will be analysed in a similar way, additionally using measures of MI community composition and diversity measures, mostly in a descriptive way.

In addition to the randomized comparison between probiotics and placebo groups, a comparison between healthy controls and patients (in both arms) will be done to assess both differences in gut MI composition and diversity between patients with AN and healthy controls in the most acute phase of disease (at admission to inpatient treatment) and to assess the size of changes during and after treatment and weight rehabilitation in patients with AN compared to natural fluctuations of MI composition in healthy adolescents during normal development. Again, mixed‐effects models repeated measures analyses with an emphasis on descriptive reporting of confidence intervals of effect sizes will be performed.

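### Neither microbiome analysis described in the plan estimates the secondary hypothesis that probiotics bring the gut microbiome closer to that of healthy individuals than placebo does

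*Protocol article*

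**What the plan says.** - **Hypothesis (section 2.1.2).** "The composition of the gut MI of patients with AN who receive probiotics gets closer to the MI of healthy individuals", with patients on placebo as the comparator. The statement involves three groups and a direction: each arm's position relative to healthy individuals, compared between arms.
- **Analysis between arms (section 2.13).** Secondary outcomes, including change in the gut microbiome, follow the approach used for BMI, "additionally using measures of MI community composition and diversity measures, mostly in a descriptive way". Controls have no stated part in this.
- **Analysis involving controls (section 2.13).** Separately from the randomised comparison, "a comparison between healthy controls and patients (in both arms) will be done". Two purposes are given: to describe how patients differ from controls at admission, and to set the size of patients' changes against the variation that healthy adolescents show over time.
- **Reference group.** The introduction expects "alterations in the MI approaching composition of healthy‐weight individuals". Section 2.3 matches the 60 controls on sex and age. Section 2.4 applies the patients' general criteria to them and adds that "they have to be absent from any current diagnosed psychiatric disorder and current or lifetime eating disorder". No BMI limit is stated.

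**The concern.** BMI has a direction, so an arm difference in BMI says which arm did better. Community composition has none. Two arms can differ clearly in composition or diversity while neither is nearer to the controls, or while the probiotics arm has moved further away. The stated arm comparison would not tell these cases apart.

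What is at stake is the reading of the trial's one explicit between-arm hypothesis about microbiome composition, in a trial whose title names the microbiome. If the contrast is not named before unblinding, the distance measure and the reference set can be chosen after the results are seen, or any arm difference can be reported as normalisation.

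**Working it through.** **1. Hypothesis against stated analyses.** Let D be a patient's distance to the healthy-control samples at a visit. The hypothesis concerns

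Δ = mean change in D on probiotics − mean change in D on placebo, with Δ < 0 expected.

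- The between-arm analysis uses no control data, so D is never formed.
- The comparison at admission precedes treatment and carries no information on Δ.
- The comparison of change with background variation concerns how large the changes are, not whether they go towards controls, and it is not described as a contrast between arms.
- If the phrase about both arms means each arm separately against controls, that gives two patient-control comparisons. Δ is the difference between them, with its own interval, and that is not stated.

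**2. Does the distinction change conclusions?** An illustrative simulation (4,000 runs per row) used assumed inputs that do not come from the documents: two dimensions; control and baseline patient SD 1; patient baseline mean 2 units from the control mean; SD of change 0.7; a probiotic shift of 0.7; two-sided alpha 0.05. The group sizes are the planned 30 per arm and 60 controls. The arm comparison of change is a Hotelling test. The distance comparison is a t-test on change in distance to the control centroid.

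| Direction of probiotic shift | Arm comparison of change significant | Distance favours probiotics | Distance favours placebo |
|---|---|---|---|
| Towards controls | 93.1% | 75.0% | 0% |
| Away from controls | 93.2% | 0% | 89.9% |
| Sideways | 93.5% | 0.8% | 7.4% |
| No shift | 6.0% | 2.5% | 2.5% |

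The arm comparison is almost equally often significant in the first three rows. Only the distance comparison separates them.

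**3. Is a distance contrast feasible at this sample size?** The plan's own figures come first (section 2.12: d = 0.75, two-sided alpha 0.10, power 80%, 24 per group).

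- Normal approximation: n = 2(1.645 + 0.842)² / 0.75² = 22 per group. The t-test gives 22.7, so 23. The stated 24 has 82% power.
- Power at 30 per group for d = 0.75, 1.0 and 0.65: 89.0%, 98.5% and 80.0%, against 88%, 98% and 80% stated. The plan's figures are reproduced closely; they concern BMI.

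For a distance outcome compared by t-test, the d detectable with 80% power is roughly (z for alpha + 0.842) × √(2/n). Exact t-test values:

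| Patients per arm | alpha 0.10 | alpha 0.05 |
|---|---|---|
| 30 (planned) | 0.65 | 0.74 |
| 27 (30 × 0.90, the plan's dropout) | 0.69 | 0.78 |
| 24 | 0.73 | 0.83 |

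These lie around the d = 0.75 assumed for BMI. They show that the contrast can be estimated about as well as the primary outcome; they do not measure the size of the problem.

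**4. Are the data there?** Table 1 schedules stool and BMI at every visit and restricts only the eating disorder interview and the autistic-trait scale to patients. Controls therefore supply both at baseline, month 6 and month 12, though not at discharge.

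**The case against.** The strongest reply is that a journal article condenses the plan. Choosing a dissimilarity measure and deriving a microbiome endpoint are ordinary SAP content, and nothing in section 2.13 rules out a distance to controls. That stands for the metric. It does not dispose of the point, because the article lists its microbiome comparisons and their purposes, and that list omits what its own hypothesis asks.

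It is also fair that a between-arm analysis of microbiome change is planned, and that this answers the title's broad question. A reader might infer that the trial cannot address the microbiome at all; the text does not support that.

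Two further inferences are tempting and go too far.

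- **The control reference is wrong because it contains underweight and overweight adolescents.** The healthy-weight wording occurs only in the introduction; the hypothesis says healthy individuals, which agrees with section 2.4. The absence of a listed BMI limit does not show who was recruited. One could calculate 0.20 × 60 = 12 controls outside the 10th to 90th BMI percentile, but that assumes volunteers found through flyers, posters and social media, and screened for psychiatric and eating disorders, mirror the reference population. The documents give no support for that, and none for a 90th-percentile bound.
- **Any arm difference is only the swallowed product.** At month 6, and at a discharge visit before then, samples can contain the product's strains. The month-12 sample comes six months after the planned intake ends, so carry-over justifies a sensitivity analysis for the earlier visits and no more.

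**Conclusion.** The point holds in a narrow form: the contrast that the microbiome hypothesis needs is missing from the analyses described, and an arm difference in composition or diversity can arise without convergence on controls, or against it. This follows from the text alone. The simulation illustrates it under assumed inputs, and its percentages are not forecasts for this trial.

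The weight is moderate. The outcome is secondary and mostly descriptive, and the primary BMI result is unaffected. An unseen SAP may already contain the contrast, in which case section 2.13 only needs to say so. On the reference group, the documents support a mismatch of wording between the introduction and the hypothesis, not a defect in control eligibility.

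**What to change.** Before unblinding, add to section 2.13:

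1. **Outcome.** For each patient and visit, the mean distance (for example Bray-Curtis or Aitchison) to the healthy-control samples. State which control visits form the reference, since controls have no discharge sample.
2. **Analysis.** The mixed model already planned, with baseline distance as covariate. Report the probiotics-placebo difference at month 6 and month 12 with its confidence interval.
3. **Sensitivity analysis for discharge and month 6.** Repeat with taxa matching the product removed. The downside is that 16S reads clustered at 0.97 identity (section 2.9) will also lose resident members of those taxa.
4. **Reference group.** Either align the introduction's healthy-weight wording with the hypothesis, or add a sensitivity analysis that restricts the reference by the BMI already measured in controls. No new entry rule is needed. Any count of controls outside a percentile range should come from the data or be labelled an assumption.

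The cost is one derived variable and a few sentences of analysis wording, with no new samples or visits. Restricting the reference by BMI would leave fewer controls in that sensitivity analysis.
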